**Fig 1 pone.0281989.g001:**
[figure not shown]
Spirit schedule. Schedule of enrolment and assessments of study 1 (Fig 1a) and study 2 (Fig 1b).

For an illustration of the research questions of this research project, see Fig 2.

**Fig 2 pone.0281989.g002:**
[figure not shown]
The aim of study 1 is to investigate the relationship between social anxiety and itch intensity. The aim of study 2 is to explore the mediating effect of neuroendocrine and inflammatory parameters in the relationship between social anxiety and itch in PS-patients.

## Materials and methods

### Study design, patient recruitment, inclusion and exclusion criteria

Study 1 is a cross-sectional observational questionnaire study to answer the first research question (whether itch and social anxiety are related in PSO-patients) and to recruit PSO-patients willing to perform suction blister sampling for study 2. Study 2 is a controlled laboratory study, in which we plan to include a selected subpopulation of high and low socially anxious PSO-patients and healthy skin controls as described below. In order to recruit participants for study 1, PSO-patients will be informed about the study by written and oral announcements, information by their dermatologists as well as via websites of German psoriasis networks. Healthy skin controls will be recruited via oral and written announcements. In case patients/healthy skin controls are interested in participation in study 1, they will be contacted by staff from the Institute of Medical Psychology of the Justus-Liebig-University of Giessen via telephone, and receive further information on the study. During this telephone call, inclusion and exclusion criteria will be checked. In order to be included in study 1, participants need to be between 18–65 years old, know the German language well enough to be able to fill in the questionnaires adequately, and in case of PSO-patients have been clinically diagnosed with PSO at least six months prior to inclusion. PSO-patients and controls with other itchy (skin) conditions such as bullous disorders are excluded. Also, individuals who currently receive or have received psychotherapeutic/ psychopharmacological treatment due to a psychological/ psychiatric disorder during the last six months are excluded. Further exclusion criteria for study 2 are a diagnosis of any transmissible disease, and treatment with biologicals, because these can interfere with neuroendocrine and immune parameter measurements [66]. In general, we strictly protocol medical and psychological conditions before inclusion and at the beginning of the examination in order to be able to assess how comorbidities affect our findings.

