### Control variables

In both studies, person-related variables (age, gender, BMI, smoking, use of oral contraceptives, and social status) will be assessed as control variables to control for standard confounding factors. The self-administered patient assessed severity index (SA-PASI) will be used in PSO-patients to measure the severity of PSO during the last 24 hours before examination [80]. In addition, the current psychological health status will be assessed in study 2 with the short form of the German Health Questionnaire for Patients (PHQ-D) [81], and general and current anxiety and depression will be assed with the State-Trait-Anxiety-Depression-Inventory (STADI) [82]. In addition, the suction-blister-pump will be applied during the time from 12 to maximally 3.30pm in order to consider the alteration of neuroendocrine and inflammatory parameters during the day [83–85].

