### Statistical analyses

Statistical analyses will be performed using SPSS and the macro PROCESS for SPSS [86–88]. In order to answer research question of study 1, Spearman’s rank-order correlation analyses will be conducted first in order to see which of the control variables are significantly related to itch intensity in PSO patients. These will then be included in step 1 of the subsequent linear hierarchical regression model. Social anxiety measured by the SIAS and SPS will be considered as predictor variable in step 2 of the analyses. Maximum and average itch intensities represent the criterion variables

To answer the research question of study 2, mediation analyses will be conducted using the SPSS macro PROCESS [86–88]. In these analyses, control variables significantly associated with itch intensity as well as social anxiety will be included as possible predictor variables, neuroendocrine and inflammatory parameters as mediators, and average as well as maximum itch intensity as criterion variables. If we find significant correlations between maximum induced itch, and the neuro-inflammatory parameters, we will exploratively conduct a regression analysis with the maximum induced itch as end-point.

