Separate analyses will be conducted for patients and controls. To determine the required sample size, we performed an analysis using G*Power [89] to extrapolate the sample size for study 2. Based on correlational studies regarding itch and anxiety [33] as well as on neuroinflammatory parameters and itch [52] in PSO-patients we expect small to medium sized effects (f^2^ = .10). The estimation with an α of 0.05 and a β of 20 revealed that 64 healthy skin controls and 64 PSO-patients are to be included in study 2. Small to moderate effects can be assumed because, on the one hand, only extreme groups are examined and, on the other hand, small to moderate correlations between anxiety and itch intensity (*r* = .179; *p* = .003) have been found in PSO-patients [33] and between neuroinflammatory parameters and itch intensity (*r* = .60; *p* < .01) [52]. In case, that patient recruitment for the studies is slower than anticipated, we would aim to gather additional personnel and material resources to improve the recruitment rate over time. Since study 2 has more strict inclusion and exclusion criteria on e.g. medication and comorbidities than study 1 (see inclusion and exclusion criteria), we expected a reduction in participants who match these premises. In addition, motivational factors are to be considered, as in contrast to study 1, study 2 will be conducted in a laboratory setting. We therefore estimated that n = 500 participants need to be included in study 1 to achieve the calculated sample size of n = 128 participants for study 2. As there is no cut-off value in the user manual of the SIAS [90] to categorize somebody as low socially anxious, we planned to use percent range ≤ 25 in order to categorize 32 participants per group as being low socially anxious. Due to the pandemic situation, participant recruitment during the course of 2020 and 2021 was and still is very difficult. Therefore, we had to change this inclusion criterion for study 2 and now invite all participants of study 1 irrespective of their social anxiety scores to take part in study 2. High and low socially anxious participants will now be identified by median split. Statistical analyses will be conducted when the targeted sample size (study 1: *N* = 500, study 2: *N* = 128) has been achieved or further inclusion of participants is no longer possible due to the end of funding. No intermediate data analysis is planned. Data collection started after ethic approval in December 2020 for study 1 (number of currently assessed patients n = 234; number of currently assessed healthy controls n = 174), and in September 2021 for study 2 (number of currently assessed patients n = 27; number of currently assessed healthy skin controls n = 15). Data collection will be continued until the planed sample sizes are reached or as long as funding is available.

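### Study 2 guards the mediators against biologicals only; other anti-inflammatory psoriasis treatment is neither excluded nor a listed control variable, so it can confound the mediator-itch path

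*Protocol article*

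**What the plan says.** All places are in the protocol article.

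- **Eligibility** (Study design, patient recruitment, inclusion and exclusion criteria): besides transmissible disease, study 2 further excludes "treatment with biologicals, because these can interfere with neuroendocrine and immune parameter measurements". No other psoriasis treatment is named. The criterion on psychological treatment in the same section does carry a period: "individuals who currently receive or have received psychotherapeutic/ psychopharmacological treatment due to a psychological/ psychiatric disorder during the last six months are excluded".
- **Recording** (same section): "we strictly protocol medical and psychological conditions before inclusion and at the beginning of the examination", so that the influence of comorbidities can be judged. Treatment is not named.
- **Control variables**: "person-related variables (age, gender, BMI, smoking, use of oral contraceptives, and social status) will be assessed as control variables". SA-PASI in patients, PHQ-D, STADI and a fixed time of day are added, and the section on itch intensity adds maximum induced itch. Psoriasis treatment does not appear.
- **Mediation model** (Statistical analyses): "control variables significantly associated with itch intensity as well as social anxiety will be included as possible predictor variables". SP, IL-6 and IL-17 are the mediators, average and maximum itch the outcomes. Patients and controls are analysed separately, so the patient model has 64 people.
- **Other mentions of medication**: Statistical analyses notes that "study 2 has more strict inclusion and exclusion criteria on e.g. medication and comorbidities than study 1", and the Discussion gives SSRIs as an example. Both point back to the eligibility section and add no drug class.

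**The concern.** The exclusion rests on a measurement argument: a drug that disturbs the mediators should not be in the sample. The argument is not specific to biologicals. The Introduction describes psoriasis as an inflammatory disease driven by T-helper 1 and 17 responses and reports that antagonists of IL-17, one of the three mediators, reduce itch in these patients. A treatment that acts on skin inflammation may therefore be a common cause of mediator and outcome.

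If some of the 64 patients receive such treatment and others do not, two results are exposed. The mediator-itch association (the b-path) may partly reflect who is treated. The patient-control difference in the mediators, which the Objectives list as a further question, would depend on the treatment mix among patients. Oral contraceptives are recorded as a potential confounder; psoriasis treatment is not. The covariate rule works on the listed variables, so it cannot repair the omission. The study 1 estimate of the anxiety-itch relation is outside this point.

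**Working it through.** **1. The plan's own figure.** Inputs from Statistical analyses: f² = .10, α = .05, β read as 20%, 64 per group. A noncentral t calculation for one regression coefficient (noncentrality² = f²·N) gives N = 64 with power .80 if one-sided; two-sided it gives N = 81. So 64 reproduces in the one-sided, single-coefficient form. Sidedness is a separate matter. As a correlation the planned effect is r = √(f²/(1 + f²)) = √(.10/1.10) = .30. The two-sided 5% critical value at n = 64 is |r| = .246.

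**2. Correlation induced by a shared treatment effect.** Assumptions, none given in the documents: a share q of patients is treated; treatment shifts mediator and itch by dM and dY within-group SDs; mediator and itch are otherwise unrelated.

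r = q(1−q)·dM·dY / √[(1 + q(1−q)dM²)(1 + q(1−q)dY²)]

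With an equal lowering d this reduces to r = q(1−q)d² / (1 + q(1−q)d²). The rejection rates come from 10,000 simulated studies per cell (n = 64, two-sided 5%, treatment unadjusted).

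| q | r, d = 0.8 | rejected | r, d = 1.0 | rejected |
|---|---|---|---|---|
| 10% | .0576/1.0576 = .05 | 6.9% | .09/1.09 = .08 | 10.3% |
| 20% | .1024/1.1024 = .09 | 11.6% | .16/1.16 = .14 | 19.5% |
| 30% | .1344/1.1344 = .12 | 15.3% | .21/1.21 = .17 | 27.8% |

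With treatment as a covariate the rate is 4.9 to 5.2% in all six cells. Outside this range, d = 0.5 gives r of .02 to .05 (rates 5 to 7%) and d = 1.5 gives .17 to .32 (27 to 76%).

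**3. Sign.** The formula depends on the product dM·dY. If treated patients have lower mediators but, because treatment was given for worse disease, still have more itch, the product is negative. With dM = −0.8 and dY = +0.8 the induced r is −.05 to −.12 over the same shares, which would hide a true positive association.

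**4. Mediation.** Joint-significance test of both paths, n = 64, q = 30%, d = 1.0, treatment unrelated to social anxiety, no true mediator-itch effect:

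- no anxiety-mediator path: false mediation 1.0% unadjusted;
- anxiety-mediator path of 0.35: 17.5% unadjusted, 3.8% with treatment as a covariate.

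**5. Patient-control comparison.** Under the same assumptions the patient mean moves by q·d: from 0.1 × 0.8 = 0.08 SD to 0.3 × 1.0 = 0.30 SD.

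**The case against.** Several objections have force.

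- **The size is assumed.** No treated share or drug effect is in the documents. Every r in the table lies below the critical .246, and with few treated patients or a small effect the bias is negligible. This stands.
- **The direction is not fixed.** A reader might infer that mixing treated and untreated patients must produce a positive mediator-itch correlation. Treatment by indication can shrink, cancel or reverse it. This stands.
- **A confounded b-path is not false mediation.** A reader might infer that the main study 2 conclusion is at risk on this ground alone. It is not: an anxiety-mediator path, or a link between treatment and social anxiety, is also needed. The first of these is, however, what study 2 hypothesises.
- **SA-PASI may absorb part of the effect.** It would be too strong to say that the planned analysis has no means of removing any of it. SA-PASI enters only if it passes the significance screen, and it does not capture an effect on the mediators that bypasses visible severity.
- **Recently stopped biologicals.** A reader might infer, from the six-month period in the psychological criterion, that such patients are eligible. The biologicals criterion does not say current, so past use could equally be read as excluded. The text is ambiguous, and the fuller protocol, not shown, may define it.
- **Topical treatment at the sampling site.** Blisters are placed at least 3 cm from lesional skin, which makes this route less likely. It does not address systemic treatment.
- **Breadth is deliberate.** The Discussion accepts moderate internal and external validity, and recruitment is difficult. That argues against wider exclusion, not against recording and adjusting.

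The article states the criterion, its reason and the control-variable list. The mismatch between them remains after all of this.

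**Conclusion.** The point holds in a limited form. The biologicals exclusion is narrower than its stated reason, and the analysis as written leaves other anti-inflammatory or immunosuppressive psoriasis treatment unadjusted, apart from whatever SA-PASI picks up. It is a plausible confounder of the mediator-itch path and of the patient-control cytokine comparison in study 2.

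Under an assumed equal lowering of 0.8 to 1.0 SD in 10 to 30% of patients, the induced r is about .05 to .17, from roughly a sixth to over half of the planned .30, and the b-path false-positive rate is about 7 to 28% instead of 5%. These figures show what is possible; they do not estimate the bias in this sample, and the sign could differ.

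The documents do not support saying that recently treated patients certainly pass screening, that the confounding by itself yields false mediation, or that a six-month window or a wider exclusion is required. This is a cheap improvement, not a flaw that invalidates the design.

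**What to change.** - Record current and recent psoriasis treatment, systemic and topical on the sampled forearm, at the study 2 telephone screen or laboratory visit. Collect it retrospectively for patients already sampled (27 of 64 when the article was written).
- Enter treatment (yes/no) as a fixed covariate in the patient mediator models, outside the significance screen.
- Repeat the mediation analysis in untreated patients. Do the same for the patient-control comparison, where a yes/no covariate helps less because controls have no psoriasis treatment.
- State what period the biologicals criterion covers. The choice is the investigators'; no window and no drug exclusion is proposed here, and nobody's treatment changes.

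The cost is one or two questions, one degree of freedom at n = 64 and one sensitivity run. The restricted analysis is smaller (at 30% treated, 64 × 0.7 ≈ 45 patients), so it should be read for consistency of the estimates, not for significance. Retrospective answers from patients already sampled are open to recall error.

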### Study procedure

The research project is divided into two studies. Study 1: After inclusion, validated self-report instruments and a consent form will be sent to the participants by mail, which they are to return to the Institute of Medical Psychology in pre-stamped envelopes provided with the package. The questionnaire sets include items to assess sociodemographic information, social anxiety and itch intensity. In case of PSO-patients participants will additionally report about the severity of their PSO. The data will be transferred to IBM® SPSS® and stored pseudonymously in line with the data protection regulations. For participation in study 1, participants are financially reimbursed. They are also asked to leave their contact details, if they are interested in participation in study 2.

Study 2: Patients and healthy skin controls will be selected from the pool of study 1, who showed interest to participate in study 2. They will be informed about the procedures involved in study 2 in a telephone conversation. In this phone call, the inclusion and exclusion criteria (see above) will be assessed. After inclusion, participants will be invited to the laboratory of the Institute of Medical Psychology. Participants will be habituated to the suction blister method by verbal instructions of the experimenter, and a demonstration of the loudness and handling of the suction pump (session 1; habituation). Participants are informed that they can withdraw from the study at any time without giving reasons. Afterwards, they give their informed consent and have a standardized lunch break before the actual induction of blisters on the skin (session 2). At the beginning of the second session in the laboratory, participants will be asked to fill in the same questionnaires as in study 1. In addition, in study 2, two further questionnaires will be deployed to assess the current psychological health, and current/ general anxiety and depression (see below). Afterwards, the suction blister pump will be used to induce blisters. This allows the collection of blister fluid and the roof of the blisters for determination of neuroendocrine and inflammatory parameters therein. In total, both sessions of study 2 will last 5.5 hours approximately. All participants will receive a financial compensation for participation in study 2. Details and unforeseen events during the trial will be protocolled by the experimenter.

### Psychometric measures

#### 1) Social anxiety

Social anxiety is measured in both studies by means of the *social anxiety disorder scales* (SOZAS) [67]. These include the *social interaction anxiety scale* (SIAS) and the *social phobia scale* (SPS). Both are validated German questionnaires, which contain 20 items each that need to be answered on a 5-point scale. The SIAS measures interactional anxiety, the SPS measures anxiety in evaluation situations. The items in both questionnaires do not refer to a specific time period. In this research project, subjects will be categorized as being either high (HSA) or low (LSA) socially anxious according to a median split of the SIAS scores in order to determine whether these groups differ in itch intensity and the secretion of assessed neuroendocrine and inflammatory parameters.

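### Testing high against low social anxiety by a SIAS median split wastes power now that selection by anxiety score is dropped, and the effect size still cites extreme groups

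*Protocol article*

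**What the plan says.** Under Psychometric measures, 1) Social anxiety, the protocol article describes SIAS and SPS as questionnaires that "contain 20 items each that need to be answered on a 5-point scale". It then states that "subjects will be categorized as being either high (HSA) or low (LSA) socially anxious according to a median split of the SIAS scores", and gives the purpose: "in order to determine whether these groups differ in itch intensity and the secretion of assessed neuroendocrine and inflammatory parameters". This is a planned comparison, not only a way of describing the sample.

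Statistical analyses gives the history. For the low group, "we planned to use percent range ≤ 25 in order to categorize 32 participants per group as being low socially anxious". Because recruitment was difficult during the pandemic, the investigators "now invite all participants of study 1 irrespective of their social anxiety scores to take part in study 2", and "High and low socially anxious participants will now be identified by median split".

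The same section still defends the effect size as follows: "Small to moderate effects can be assumed because, on the one hand, only extreme groups are examined". The study design section also still describes study 2 as a selected subpopulation of high and low socially anxious participants.

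For the main questions, Statistical analyses enters social anxiety, measured by SIAS and SPS, in step 2 of a hierarchical regression (study 1) and as a predictor in PROCESS mediation models (study 2). Neither description mentions a split. Patients and controls are to be analysed separately.

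**The concern.** High and low groups are a sensible contrast when only the tails of a score are recruited: the groups lie far apart and the middle is absent. Once everyone is invited, most participants score near the middle. A cut at the median then puts people with almost equal scores in opposite groups and treats a score just above the median like the highest in the sample. A 20-item scale is reduced to one binary variable.

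Two things are at stake. First, the HSA/LSA comparisons of itch and the three mediators have less power than the same data allow. Second, the effect-size argument still claims a benefit from extreme groups that the current design no longer has, so a reader of the sample-size paragraph is told the opposite of what the split does.

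**Working it through.** **Inputs from the article (Statistical analyses).** f² = .10; α = .05, sidedness not stated; β printed as 20, read as .20; 64 patients and 64 controls, analysed separately; cited anxiety–itch correlation r = .179; study 1 target of 250 patients.

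**Assumptions.** f² = .10 is the effect on the continuous score; the relation is linear; SIAS is normal in the base case. The article does not give the SIAS distribution, so other shapes are shown below.

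**1. The plan's own figure.** Test of one regression coefficient, noncentral t with ncp = √(f²·N) and df = N − k − 1. At N = 64, ncp = √6.4 = 2.53.
- One-sided α = .05: smallest N for 80% power is 64 (power .804). This reproduces the planned number.
- Two-sided α = .05: smallest N is 81; power at 64 is .702.

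Both versions are carried forward.

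**2. Attenuation by the split.** For a standard normal score, the correlation between the score and its above-median indicator is φ(0)/0.5 = .3989/.5 = √(2/π) = .798. Relative efficiency is .798² = 2/π = .637, a loss of 36%. In round terms, 64 participants do the work of 64 × .637 ≈ 41.

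**3. Effect on f² and power.**
- R² = f²/(1 + f²) = .10/1.10 = .0909, so r = .302.
- After the split: r = .302 × .798 = .241.
- f² = .241²/(1 − .241²) ≈ .061.
- ncp at N = 64: √(.0614 × 64) = 1.98.

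| f² = .10 on the continuous score | Continuous SIAS | Median split |
|---|---|---|
| Power at n = 64, one-sided | .80 | .62 |
| Power at n = 64, two-sided | .70 | .50 |
| N per population for 80%, one-sided | 64 | 103 |
| N per population for 80%, two-sided | 81 | 130 |

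The N values are totals per population: 130 means 65 high and 65 low.

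**4. What extreme groups would have given.** The article states a cut only for the low group; the upper quartile for the high group is my assumption. With outer quartiles of a normal score:
- cut c = .674, tail mean m = φ(c)/.25 = 1.271, within-tail variance 1 + cm − m² = .242;
- d = 2 × 1.271 × .302/√(1 − .0909 + .0909 × .242) = .79;
- group correlation .369, f² = .158.

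Power at n = 64 would be .93 one-sided or .88 two-sided. Tail sampling raises the effect above the continuous unselected analysis; the median split lowers it below.

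**5. Sensitivity to the shape of SIAS.** Information lost by a median split:

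| Assumed shape | Loss |
|---|---|
| Uniform | 25% |
| Normal | 36% |
| Gamma, shape 4 | 41% |
| Gamma, shape 2 | 45% |
| Exponential | 52% |

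Right skew makes the loss larger.

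**6. At the cited r = .179, two-sided.** With n = 64, power is .30 continuous and .21 split. With the 250 study 1 patients it is .82 continuous and .62 split. The split figures describe only an HSA/LSA comparison of itch.

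**The case against.** The strongest reply is that little depends on the split. The two research questions are answered by hierarchical regression and mediation, and neither mentions groups. The mediation models also estimate the paths from social anxiety to SP, IL-6 and IL-17. This stands, and it limits the reach of the point. A reader might infer from the .82 and .62 that study 1 is underpowered, or from the .70 and .50 that the mediation analysis is. The article does not support either inference: the lower figures belong to the HSA/LSA comparisons alone. But if the models already use the scores, the group tests add only a weaker second answer to the same question, which may disagree with the first.

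A reader might also infer that HSA/LSA is confounded with diagnosis, if the median is pooled and patients are more anxious. The article does not support this. Patients and controls are analysed separately, so a pooled median could only make the groups unequal within each population. The objectives ask whether patients and controls differ in social anxiety without stating a direction. Where the median is taken is a detail that a condensed article may leave to the full plan.

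The article is also open about why the rule changed and about the lack of a manual cut-off for low social anxiety. That explains why the tail rule was given up. It does not explain why groups are still needed as a test once everyone is invited, and it does not rescue the extreme-groups sentence.

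Finally, the size of the loss depends on a distribution that the article does not give. That is correct, and a range is therefore shown. At every shape tried, the split loses at least a quarter of the information.

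**Conclusion.** The point holds for the planned HSA/LSA comparisons of itch, SP, IL-6 and IL-17, and for the sample-size rationale. Under a normal SIAS and a linear relation, the split loses about 36% of the information (25% to 52% across the shapes tried). With f² = .10 on the continuous score and 64 per population, power drops by about 20 percentage points two-sided (.70 to .50) and 18 one-sided (.80 to .62). If f² = .10 was instead meant as the effect in extreme groups, the effect in an unselected sample would be smaller and these powers would be optimistic.

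Separately from any assumption, the sentence that only extreme groups are examined contradicts the same section's statement that all study 1 participants are invited whatever their score.

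This is a change that should be made; it does not threaten the main models.

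**What to change.** - In 1) Social anxiety and in Statistical analyses, replace the HSA/LSA tests by regressions of itch, SP, IL-6 and IL-17 on continuous SIAS, separately in patients and controls. A spline term can serve as a check on linearity.
- Keep HSA/LSA for descriptive tables only, and say so.
- Delete the extreme-groups reason for the effect size, and bring the description of study 2 in the study design section into line with open invitation. The support for f² = .10 then rests on the two cited correlations. These imply very different values: .179²/(1 − .179²) = .033 for r = .179 and .36/.64 = .56 for r = .60. The choice of .10 therefore needs a sentence of its own.

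Cost: wording only. No new data or visits are needed, and since no intermediate analysis is planned, the change can be recorded before results are examined. The downside is that simple two-group contrasts are no longer available as tests.
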